### 8.3.5 Adverse Event Reporting

The reporting of AEs and SAEs will start when the patient signs the informed consent for the study throughout the treatment period and up to and including the 28-day follow-up period. All new AEs occurring during that period must be recorded (if SAEs, they must be reported to the Data Safety Monitoring Committee (DSMC) and IRB as per institutional guidelines). AEs will be recorded per SOPs.

The investigator will report the action taken with study agent as a result of an AE or SAE, as applicable (e.g., discontinuation, interruption, or dose reduction of study agent, as appropriate) and report if concomitant and/or additional treatments were given for the event.

- Patients receiving treatment with dronabinol capsules should be alerted to the potential for additive central nervous system depression if dronabinol capsules is used concomitantly with alcohol or other CNS depressants such as benzodiazepines and barbiturates.

Study agent will be discontinued for all AEs grade 3 or above. Study agent will not restarted until AE has resolved to grade 1 for all objective events or until patient grade 1 or grade 2 and patient requests to restart drug despite symptoms for all subjective events. This is because some adverse events of dronabinol may be seen as a benefit by patients, for example dronabinol may cause tiredness but some patients with SCD complain of insomnia.

Study agent will not be discontinued for expected AEs or SAEs determined to not be due to dronabinol such as a pain crisis.

For patient reported AEs grade 1 or 2 the patient and investigator will decide together whether to discontinue study agent, lower the dose of study agent, or to continue on full dose if the patient feels that the benefit of study agent outweighs the discomfort of the AE of the AE is in fact perceived as a benefit (i.e. sleepiness may be a benefit if the subject previously suffered from poor sleep).

The investigator will report the outcome of the event for both AEs and SAEs. All SAEs that have not resolved upon discontinuation of the subject’s participation in the study must be followed until recovered (returned to baseline), recovered with sequelae, or death (due to the SAE)

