 Coordinator will ask the participant to continue to attend all study visits and complete assessments. Criteria for discontinuation of the randomization condition include 1) pregnancy; 2) current suicidal ideation with plan or intent; 3) suicide attempt; 4) severe anxiety episode, severe depression episode, or psychotic symptoms; 5) severe adverse events probably or definitely related to the randomization condition, as defined above; 6) adverse events that have the potential to cause serious impairment of health, including ischemic or arrhythmic adverse cardiovascular disease events (e.g., myocardial infarction, unstable angina, coronary revascularization, coronary artery disease, unstable arrhythmias, transient ischemic attack, stroke, or congestive heart failure); 7) serious adverse events, defined as those which result in death, are life threatening, require inpatient hospitalization or prolongation of existing hospitalization, result in significant disability or incapacity, or result in congenital anomaly or birth defect; or 8) the request of participants or their treating providers. [name] or the Study Coordinator will be responsible for informing the participant to discontinue the randomization condition and will ask the participant to continue to attend all study visits. Once the randomization condition has been discontinued it will be for the duration of the study.

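### Sections 7.1 and 8.3.5 conflict: 8.3.5 lets staff continue or restart study drug in participants whom 7.1 stops for the rest of the study

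*Protocol*

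**What the plan says.** Protocol section 7.1 (Discontinuation of Study Intervention) gives a numbered list of criteria for stopping the randomized treatment. Criterion 4 is "severe anxiety episode, severe depression episode, or psychotic symptoms". Criterion 5 is "severe adverse events probably or definitely related to the randomization condition", followed by a reference back to an earlier definition. The section closes with: "Once the randomization condition has been discontinued it will be for the duration of the study".

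Protocol section 8.3.5 (Adverse Event Reporting) handles study drug by adverse event grade:

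- **Grade 3 or above:** "Study agent will be discontinued for all AEs grade 3 or above". Restart conditions follow. For objective events, "Study agent will not restarted until AE has resolved to grade 1 for all objective events". For subjective events, the event must have come down to grade 1 or 2 and the condition is that the "patient requests to restart drug despite symptoms for all subjective events".
- **Grade 1 or 2, patient-reported:** "For patient reported AEs grade 1 or 2 the patient and investigator will decide together whether to discontinue study agent". The alternatives are a lower dose, "or to continue on full dose if the patient feels that the benefit of study agent outweighs the discomfort of the AE", or full dose where the event itself is felt to be a benefit.

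Section 8.3.5 does not mention 7.1 and has no exception for psychiatric events.

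**The concern.** Criterion 4 attaches the word severe separately to anxiety and to depression and leaves it off psychotic symptoms. The natural reading is that psychotic symptoms of any severity end treatment, permanently. Section 8.3.5 makes a stop mandatory from grade 3 upward, leaves patient-reported grade 1 or 2 events to a joint decision, and allows for restart after the mandatory stop. Staff handling an adverse event are likely to turn to 8.3.5, and nothing there sends them to 7.1.

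What is at stake is participant safety. The case is foreseeable: section 2.3.1 lists paranoid reaction among the most common side effects, and the structured adverse event interview in 8.2 asks about paranoid thoughts. Section 5.2 excludes people with a history of psychosis. That should make such events rarer, but it does not deal with new symptoms on drug, which is the situation criterion 4 addresses.

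**Working it through.** The protocol states no figure on this point, so the check is to apply both sections to the same participant.

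| Case | Under 7.1 | Under 8.3.5 |
|---|---|---|
| A. Patient-reported psychotic symptom, grade 1 or 2 | Stop, for the rest of the study (criterion 4) | Joint decision: stop, reduce, or stay at full dose |
| B. Psychotic symptom of grade 3 or above that later improves | Stop, for the rest of the study (criterion 4) | Stop, then restart possible at grade 1 (objective), or at grade 1 or 2 on the patient's request (subjective) |
| C. Severe event, probably or definitely related, that later improves | Stop, for the rest of the study (criterion 5) | Same restart conditions as B, if severe means grade 3 or above |

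Case A depends on reading the missing qualifier as any severity. Case B does not, because the event is severe on any reading. Case C depends on equating severe in criterion 5 with grade 3. Section 8.3.3.1 labels grade 3 as severe, but in the fallback scale for events outside the main grading system. The back-reference in criterion 5 does not settle the matter, because what 7.1 defines earlier is serious events, not a grade. The equation is plausible but is an inference.

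In all three cases one section ends treatment and the other allows it to go on or resume.

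**Exposure at stake for one participant.** Inputs: treatment lasts 8 weeks (section 4.2); adverse events are assessed at weeks 2, 4, 6 and 8 (section 8.2). For an event found at week w, the share of treatment left is (8 − w)/8:

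- week 2: (8 − 2)/8 = 6/8 = 75%
- week 4: (8 − 4)/8 = 4/8 = 50%
- week 6: (8 − 6)/8 = 2/8 = 25%

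These are upper limits. In cases B and C the difference is the remaining weeks less the interruption before restart. The protocol gives no frequency for these events, so an expected number of participants cannot be calculated.

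**The case against.** The best defence is that the sections can be read together. Section 7.1 is the dedicated discontinuation section and its list is specific, so it should override general advice on grades. The restart wording is a minimum condition and entitles nobody to restart. Section 8.3.5 elsewhere separates discontinuation from interruption, so its grade 3 rule might be an interruption rule. Stopping permanently breaches nothing in 8.3.5, since discontinuation is one of its options. The investigator can refuse to continue, section 7.2 lets any investigator end participation in the subject's interest, and section 8.2 requires immediate clinical intervention for a new psychiatric diagnosis or suicidal ideation.

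Part of this stands. A compliant path exists, other safeguards exist, and 8.3.5 never requires continuation or restart. But the protocol does not say that 7.1 overrides 8.3.5. Section 8.3.5 uses the word discontinued for the very stop it then allows to be reversed, and it justifies restart on the ground that some effects may be welcome to patients. Restart is therefore intended. Discretion to stop is also weaker than a rule that requires it.

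Two stronger readings are not supported:

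- A reader might infer that drug may be restarted whatever caused the event. Directly after the restart conditions, 8.3.5 says that drug is not stopped for expected events, or for serious events judged not due to dronabinol. For events covered by that sentence, restart does not arise.
- A reader might infer that every mild paranoid thought on drug must already end treatment under 7.1. The protocol does not say whether such thoughts count as psychotic symptoms.

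**Conclusion.** The conflict is real and should be corrected. As written, staff following 8.3.5 could continue or restart dronabinol in a participant whom 7.1 stops permanently, and no rule of precedence resolves it. The firmest ground is a psychotic symptom of grade 3 or above that improves. The mild case rests on the natural reading of the missing qualifier in criterion 4, and the severe related case on taking severe to mean grade 3 or above.

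The size is up to 75%, 50% or 25% of the 8-week treatment for one participant, depending on when the event is found, and no claim about the number of participants can be made. The point concerns a safety rule. It leaves the sample size and the primary analysis as they are: that analysis follows allocation, and 7.1 asks participants who stop drug to keep attending visits.

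**What to change.** Add to section 8.3.5: *The discontinuation criteria in section 7.1 take precedence over the grade-based, restart and shared-decision rules in this section; study agent stopped under 7.1 is not restarted.*

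In the same change, clarify two terms in 7.1:

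- What counts as psychotic symptoms, and in particular whether mild paranoid thoughts do.
- That severe in criterion 5 means grade 3 or above.

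The definition of psychotic symptoms should not be left for later. Paranoid reaction is listed as a common effect of dronabinol. If mild forms count, the precedence sentence would turn a common effect into a permanent stop, mostly on active drug, with unequal discontinuation between arms and a possible clue to allocation.

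The cost is a short text amendment with no new procedures or data. The downside is that some participants, more likely on active drug, lose the option to continue or restart; their number cannot be estimated from the protocol.

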### 8.3.7 Reporting Events to Participants

### 8.3.8 Events of Special Interest

### 8.3.9 Reporting of Pregnancy

## 8.4 Unanticipated Problems

### 8.4.1 Definition of Unanticipated Problems (UP)

The Office for Human Research Protections (OHRP) considers unanticipated problems involving risks to participants or others to include, in general, any incident, experience, or outcome that meets all of the following criteria:

- Unexpected in terms of nature, severity, or frequency given (a) the research procedures that are described in the protocol-related documents, such as the Institutional Review Board (IRB)-approved research protocol and informed consent document; and (b) the characteristics of the participant population being studied;
- Related or possibly related to participation in the research (“possibly related” means there is a reasonable possibility that the incident, experience, or outcome may have been caused by the procedures involved in the research); and
- Suggests that the research places participants or others at a greater risk of harm (including physical, psychological, economic, or social harm) than was previously known

### 8.4.2 Unanticipated Problem Reporting

The investigator will report unexpected problems involving risks to subjects or others (UPIRSO) to the IRB per institutional SOPs.

### 8.4.3 Reporting Unanticipated Problems to Participants

# 9 Statistical Considerations

## 9.1 Statistical Hypotheses

- Primary Efficacy Endpoint(s):

Hypothesis: Participants who receive dronabinol will have an improvement in pain impact (primary outcome) at 8 weeks compared to patients who receive placebo.

- Secondary Efficacy Endpoint(s):

Hypothesis: Participants who receive dronabinol will have improvements in other measures of pain (average daily opioid use, neuropathic and nociceptive pain severity, health care utilization, and self-reported episodes of pain crisis) and quality of life (stiffness, sleep, emotional impact, and social impact) at 8 weeks compared to participants who receive placebo.

Hypothesis: Patients who receive dronabinol will have an increase in anti-inflammatory markers (IL4, IL10) reduction in pro-inflammatory markers (all others) at 8 weeks compared to patients who receive placebo.

Hypothesis: Participants in the dronabinol group will report greater incidence of low-grade adverse events such as dizziness or nausea but no greater serious AEs (cognitive function) compared to participants in the placebo group.

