# 1 Protocol Summary

## 1.1 Synopsis

| **Title:** | Dronabinol for the reduction of chronic pain and inflammation in people with sickle cell disease |
| --- | --- |
| **Study Description:** | A randomized, double blind, study of dronabinol as a palliative agent in the treatment of pain, inflammation, and other complications of sickle cell disease (SCD). |
| **Objectives:** | \| Primary Objective: \| To determine whether dronabinol will improve pain and QOL in adults with SCD and chronic pain. \| \| --- \| --- \| \| Secondary Objectives: \| To assess dronabinol’s effect on markers of inflammation in patients with SCD compared to placebo.  To determine the safety and tolerability of dronabinol use in adults with SCD compared to placebo. \| |
| **Endpoints:** | \| Primary Endpoint: \| Change in PROMIS pain impact score \| \| --- \| --- \| \| Secondary Endpoints: \| - ASCQ-Me survey domains for emotional impact, social impact, stiffness, and sleep as well as Patient Reported Outcome Information System (PROMIS) domains for pain impact, neuropathic pain, and nociceptive pain and Leeds assessment of neuropathic signs and symptoms - WBC with differential, CRP, tryptase, substance P and cytokines IL1a, IL1b, IL6, IL4, IL10 and tumor necrosis factor alpha (TNFα). - Self-reported adverse effects, PROMIS domains for anxiety, appetite, nausea, and cognitive function, opioid use in oral morphine equivalents (OME), episodes of emergency room, hospital, or psychiatric facility utilization, Columbia suicide severity rating scale, prodromal questionnaire brief version \| |

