## 9.2 Sample Size Determination

In a study examining the responsiveness of PROMIS pain impact to changes in chronic pain patients who stated pain was a “little better” had an average increase of 1.8 point with a SD of 6.6 points and “much better” was associated with an average increase of 6.8 points with a SD of 6.5 points.^65^  Based on this we have chosen a change of 5 points as representing a clinically meaningful improvement in chronic pain, with an estimated a SD of 6.5 points. With a sample size of 28 patients (56 total) in each group we will have 80% power to detect a difference of 5 points in change between two groups in pain impact score from baseline at a two-sided 0.05 significance level.

We have a strong track record of following subjects with chronic pain, opioid use, and SCD in ourprior SCD studies have achieved 85-100% retention at 6 months. In our pilot trial we approached 27 patients to enroll 6 on study, we therefore estimate if we approach 280 patients, we can enroll 70. We conservatively estimate a 20% attrition rate, so we will aim to approach 280 patients to enroll 70 to ensure 56 participants completing the study.

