## 9.4 Statistical Analyses

### 9.4.1 General Approach

We will first conduct descriptive and graphical analyses to check for outlier and abnormal values, verify that distribution of measures meets assumptions of planned statistical tests, and explore the success of randomization. Primary analyses for all aims will be intent-to-treat analyses of data from baseline to week 8, based on group allocation. Secondary analysis will be done removing patients who do not complete at least 4 weeks on study as well as any patients whose urine samples show presence of cannabinoid metabolites other than THC or whose pill counts reveal they took less than 50% of the reported optimized dose.

Statistical analysis will be done assuming all data is non-normal. Continuous data will be described as means and quartiles, categorical data will be described as percentages.  All inferential tests will be two-tailed.

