### 9.4.4 Safety Analyses

Patients with SCD will be expected to have laboratory abnormalities and diagnoses of clinical or psychiatric conditions at baseline.  Comparison will be of new adverse events, complaints, or diagnosis in those on dronabinol to those on placebo.  The number and the percentages of patients experiencing new adverse events will be tabulated by study arm. Comparisons will be made using Fisher’s exact tests for each individual adverse event reported when appropriate.

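### Section 9.1 hypothesises no excess of serious adverse events, but the final analysis stated is event-by-event two-tailed testing for a difference, which cannot support that claim

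*Protocol*

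**What the plan says.** The Synopsis (1.1) gives a neutral secondary objective: "To determine the safety and tolerability of dronabinol use in adults with SCD compared to placebo". Section 9.1 turns it into a directional hypothesis. Low-grade events are expected to be more frequent on dronabinol, "but no greater serious AEs (cognitive function) compared to participants in the placebo group".

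The matching analysis is in 9.4.4. Numbers and percentages of patients with new adverse events are tabulated by arm, and then: "Comparisons will be made using Fisher’s exact tests for each individual adverse event reported when appropriate". Section 9.4.1 adds: "All inferential tests will be two-tailed". Section 9.3 defines the safety set as everyone who took at least one dose.

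Section 9.2 sizes the trial on pain impact only. It states no power or precision for safety and no expected SAE rate. The 0.05 level it names belongs to the pain comparison.

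Two other places bear on the point. Section 9.4.6 has an interim rule that stops the trial if SAEs are significantly more frequent on the active arm, and separately lets the research team and the DSMC stop for an unacceptable pattern of events. The Schedule of Activities (1.3) and Section 3 list cognitive function as a PROMIS survey domain; Section 3 analyses it as change from baseline.

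**The concern.** The hypothesis says there is no excess, whereas the test looks for a difference. If the test is not significant, the data may be compatible with no excess, with a large excess, or with both. The result alone does not say which, and 9.4.4 states no interval or bound that would.

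Two features make this worse. Serious events are compared term by term, so the events in each comparison are fewer than the total number of SAEs. Section 8.3.2 also keeps admissions for uncomplicated pain crisis out of the SAE definition, which lowers the count further. In addition, the hypothesis puts cognitive function in parentheses after serious AEs as though it were an event. It is a continuous score, so the event analysis cannot address it.

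What is at stake is the safety conclusion. Section 2.3.3 says that poor safety or tolerability would matter to patients and clinicians weighing other cannabis-containing products. A report of no greater serious harm that rested on non-significant Fisher tests would be unsupported.

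**Working it through.** **1. Reproduce the plan's own figure.** Section 9.2: "With a sample size of 28 patients (56 total) in each group we will have 80% power" for a 5-point difference with SD 6.5, "at a two-sided 0.05 significance level". Noncentrality = (5/6.5) × √(28/2) = 2.878 on 54 degrees of freedom, which gives power 0.807. The figure is right for a t-test, but it concerns pain only.

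**2. Size of the safety set.** "We conservatively estimate a 20% attrition rate"; 56/0.8 = 70, matching "so we will aim to approach 280 patients to enroll 70 to ensure 56 participants completing the study". At 1:1 allocation, 70/2 = 35 per arm. Since the safety set is all dosed patients, about 35 per arm is the relevant size, and 28 is the completer count.

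**3. Assumptions.** Alpha 0.05 two-sided for safety. Placebo rates of 2% to 15% for whatever is compared, whether a single term or all SAEs pooled.

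**4. Chance of missing a true excess.** For arms of size n with X ~ Bin(n, p_D) and Y ~ Bin(n, p_P), the chance of flagging is the sum of P(X=x)·P(Y=y) over all pairs with x > y and two-sided Fisher p ≤ 0.05. The chance of missing is 1 minus that.

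| Placebo vs dronabinol | Flagged, 35/arm | Missed, 35/arm | Missed, 28/arm |
|---|---|---|---|
| 2% vs 6% | 0.9% | 99.1% | 99.7% |
| 2% vs 8% | 3.0% | 97.0% | 98.7% |
| 5% vs 15% | 13.6% | 86.4% | 92.2% |
| 5% vs 20% | 32.8% | 67.2% | 79.3% |
| 10% vs 30% | 45.5% | 54.5% | 66.8% |
| 10% vs 40% | 78.5% | 21.5% | 34.1% |
| 15% vs 45% | 72.7% | 27.3% | 38.7% |

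At 35 per arm the chance of flagging reaches 50% at a placebo rate of about 10.8% for a three-fold excess and about 6.6% for a four-fold excess. Both ratios are therefore missed more often than not only at about 6.5% or below.

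**5. Smallest significant split with no placebo events.** At 35 per arm, p = 2 × C(35,k)/C(70,k).
- k = 5: 2 × 324,632/12,103,014 = 0.054, not significant.
- k = 6: 2 × 1,623,160/131,115,985 = 0.025, significant.

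So six dronabinol events against none are needed. A 4 v 1 split gives p = 0.36.

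**6. What an interval would show at 35 per arm.** Newcombe upper limit = d + √[(u₁ − p₁)² + (p₂ − l₂)²], where l and u are Wilson limits.
- 1 v 1: d = 0, upper limit 11.9 points.
- 2 v 2: d = 0, upper limit 13.5 points.
- 4 v 2: p₁ = 0.1143, u₁ = 0.2595, p₂ = 0.0571, l₂ = 0.0158. Upper limit = 0.0571 + √(0.1452² + 0.0413²) = 0.208, or 20.8 points. Fisher p = 0.67.

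**The case against.** The strongest reply is that the protocol nowhere says a non-significant test establishes safety. Section 9.4.4 begins with counts and percentages and adds the tests only where appropriate, so the plan as written yields a table and p-values. Margins, interval methods and pooled SAE tables are commonly left to a statistical analysis plan. The hypothesis is one sentence in a phase 2 protocol whose stated safety objective is neutral. Section 9.4.6 does treat SAEs as a class.

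Much of this stands. The absence of a margin or interval is not in itself an error here, and a reader who infers that the protocol adopts p > 0.05 as proof of no excess goes beyond its text. What remains is that the protocol fixes both the hypothesis and the test, and they do not fit. An analysis plan that follows 9.4.4 inherits the mismatch, and no other final analysis is stated for judging the hypothesis. The interim rule names no test and also rests on significance, so it does not supply one.

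A reader might also infer that the plan would miss a three- to four-fold excess whatever the background rate. The table contradicts that: at 10% vs 40% the excess is flagged 78.5% of the time.

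Nor do the figures show that cognitive harm would usually be missed. For an assumed worsening of 0.5 SD at 35 per arm, a t-test has power 0.541, or 0.521 with rank-sum efficiency 0.955, so detection is slightly likelier than not. The protocol does not clearly assign a test to that score in any case.

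**Conclusion.** The point holds as a mismatch between a stated no-excess hypothesis and a stated set of tests for difference. It needs no outside figure.

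Its size depends on a placebo rate that the protocol does not give. With alpha 0.05 and about 35 per arm assumed, an excess of three- to four-fold usually goes unflagged at placebo rates of about 6.5% or less, and not generally above that. Low rates are the more plausible case for individual serious terms, given the exclusion of uncomplicated pain-crisis admissions, but that is a judgement and not a figure from the protocol. The cognitive part of the hypothesis is a separate defect: a score has been placed under events, where Fisher's test cannot reach it.

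The efficacy analysis is unaffected.

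**What to change.** In 9.1, restate the safety aim as estimating the excess risk of SAEs on dronabinol relative to placebo, and list cognitive function separately as a PROMIS score.

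In 9.4.4:
- Make the main safety comparison the proportion of dosed participants with any SAE, pooled over terms, as a risk difference with a 95% CI (Newcombe, for example).
- Give the between-arm difference in PROMIS cognitive function with its CI.
- Keep the per-event Fisher tests as descriptive.
- State that a non-significant result is not evidence of no excess, and that the size of excess not excluded will be reported.

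Keeping the no-excess claim and tying it to a fixed margin is not realistic at this size. For illustration, an assumed 10-point margin at one-sided 0.025 would need about 75 per arm at a 5% rate and 142 at 10%.

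The cost is a few sentences and one table, with no extra patients or data. The price is candour: with 1 v 1, 2 v 2 or 4 v 2 SAEs at 35 per arm, the report would have to say that an excess of about 12, 14 or 21 percentage points is not excluded.
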